### Qualitative data analysis

The qualitative data will be managed using NVivo. NVivo is a software program used for qualitative and mixed-methods research. NVivo helps qualitative researchers to organise, analyse and find insights in unstructured or qualitative data where deep levels of analysis are required (67). For realist approaches, NVivo offers a framework to structure and organise the iterative process of generating, refining, and testing complex program theories, especially when drawing on multiple data sources simultaneously (68). This is particularly beneficial given the multifaceted and dynamic nature of realist data (68). Qualitative data will be transcribed, organised, and labelled using Microsoft Word.

There are different ways of coding and reporting data, holistic coding, referential coding, and axial coding (38). For holistic coding, a single code is applied to a large unit of data and is most applicable when the researcher has a general idea of what to investigate in the data. In referential coding, researchers identify and code specific phrases in the data, focusing on instances where participants explicitly or implicitly refer to certain concepts, themes, and ideas. Thirdly, axial coding involves the breakdown and categorisation of data into specific themes, concepts, or categories based on their relationships (69). By exploring Context-Mechanism-Outcome relationships allows for a more in-depth analysis of how various elements interrelate and enables the identification of patterns that contribute to improved conceptual clarity. This evaluation will be based on the latter approach.

Transcribing and coding will be piloted following a few interviews to clarify the approach. The analytical process in realist methodology is iterative, meaning that coding and analysis can be started as data are collected (38). For interview, data analysis will be based on thematic analysis and survey data, we will adopt utilise content analysis. Using data to support, refute, and refine program theories, we will primarily focus on extrapolating the lines of association (46). The results will support inferences about varied influences operating within a specific CMO configurations. Labelled CMO configurations will attempt to explain how and why various mechanisms are activated or not in different contexts to generate different outcomes (34). CMO configurations are about specific characteristics of the program, and when considered as a whole, they become the product of the complete review (70). As new theories supporting causal insights emerge during data analysis, they will be articulated and labelled accordingly. Regular fortnightly meetings with academic supervisors will be held throughout the research process to check and validate analysis process, review overall progress, and address challenges.

### Step 5: present the research output

*(Present configured contexts and mechanisms into refined program theories)*.

In this phase the refined and evidence-informed theories to support “what works, for whom, under what circumstances, how and what did not work” about the DIvERT intervention will be presented (42). Refined theories will be presented with corresponding CMO configurations. Refined theories will guide future DIvERT program design and implementation. As pointed out, propositions for policy and practice should be explained clearly, follow logically from the analysis, and recommendations should account for strategies for different contexts (46). It is prudent for realist evaluations to be modest about evaluation claims, as evaluation results cannot be universally applicable. Rather, results should provide plausible explanations for the complex processes underlying programs (42).

We will engage with key stakeholders in the final stages of the realist evaluation, an important step that serves dual objectives. Firstly, engagement provides a means to validate the research findings, aligning them with the practical experiences and perspectives of those directly involved. This validation not only improves the credibility of the evaluation but also ensures that the results align with the stakeholders’ intentions of DIvERT. Secondly, engaging stakeholders facilitates a dynamic exchange of insights, enriching the understanding of contextual nuances that may influence the success of DIvERT. The collaborative process improves the applicability of the evaluation's recommendations, fostering stakeholder buy-in and promoting the effective implementation of evidence-based strategies in other clinical settings. As per reporting standards, strengths and limitations of the methodology, utility, and analysis will be reported (46).

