## Objective

In accordance with the realist evaluation methodology, the objectives of this research are:
1.Theory articulation: Hypothesise the DIvERT program purpose by theorising, classifying and organising the assumptions of the program designers and implementers into initial program theories.2.Theory refinement: Search, review and synthesise the literature for existing empirical evidence on what works, for whom, under what circumstances, and to what extent when managing mental state deterioration in patients in acute general hospital settings.3.Theory verification: Analyse evidence to determine the contexts, mechanisms of action, and outcomes of the DIvERT program.4.Theory refinement: Present refined program theories with the corresponding context, mechanism, and outcome configurations to explain the DIvERT program and account for what did not work.5.Interpretive meeting with key stakeholders at the conclusion of a realist evaluation to validate findings, refine program theories, identify unintended consequences, gather contextual insights, provide practical recommendations, and improve the credibility of evaluation.

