**Figure 2 F2:**
[figure not shown]
Realist synthesis steps.

Refined program theories are intended to highlight the underlying generative mechanisms that contribute to the effectiveness of the rapid response team model in effectively addressing MSD. In addition, theories will consider the contextual factors that influence the implementation and effectiveness of the response model (53). The refined program theories resulting from the synthesis will be shared with the program designers within the organisation as part of the theory gleaning process. This collaborative step involves engaging with the program designers to examine and evaluate the refined theories to determine and prioritise theories for further testing in the next stage of the evaluation (51, 53). Program designers will review and provide input on the refined program theories during the theory gleaning process. Based on their expertise and knowledge of the intervention, they will evaluate whether theories are aligned with their initial assumptions and expectations (54). The objective is to gain deeper insights from program designer perspectives and determine which theories are most plausible and worthy of further testing. Through this collaborative engagement, the program designers can contribute valuable insights and identify potential additional contextual factors, mechanisms, or outcomes (53, 54). Discussions and feedback gained from the theory gleaning process will assist in refining the theories further, identifying additional contextual factors, mechanisms, and outcomes, and planning the design of data collection methodologies for the next phase (52, 54). Refined program theories are intended to highlight the underlying generative mechanisms that contribute to the effectiveness of the rapid response team model in effectively addressing MSD. In addition, theories will consider the contextual factors that influence the implementation and effectiveness of the response model (53).

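### Step 5 makes agreement with stakeholders' intentions a goal of validating the results, which risks bias towards the program's own assumptions

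*Protocol article*

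**What the plan says.** **Step 5 (Step 5: present the research output).** Key stakeholders are engaged in the final stages, with two stated purposes. The first is to validate the findings by "aligning them with the practical experiences and perspectives of those directly involved". The article then states: "This validation not only improves the credibility of the evaluation but also ensures that the results align with the stakeholders". What is to be matched comes at the end of that sentence, whose last clause in full is "also ensures that the results align with the stakeholders’ intentions of DIvERT". The second purpose is an exchange of insights about context, with stakeholder buy-in named as a benefit. The same section opens by undertaking to present failures as well as successes.

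**Objective.** Objective 4 is to present refined theories and "account for what did not work". Objective 5 describes the closing interpretive meeting. Its listed tasks include validating findings, refining the program theories and looking for unintended consequences.

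**Step 2 (text after Figure 2).** Theory gleaning consists of "engaging with the program designers to examine and evaluate the refined theories to determine and prioritise theories for further testing in the next stage". On the designers' role the article says that "Program designers will review and provide input on the refined program theories during the theory gleaning process", and that "they will evaluate whether theories are aligned with their initial assumptions and expectations". The stated aim is to gain the designers' perspectives and to "determine which theories are most plausible and worthy of further testing".

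**The concern.** A validation step should be able to show that a finding is wrong, or that it is right even though it is unwelcome. If success is defined as agreement with what stakeholders meant DIvERT to do, a correct finding that DIvERT did something else counts as a validation failure. The incentive runs in one direction, towards the program's assumptions.

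The consequences go beyond the report. Step 5 says the refined theories will guide later design and implementation of DIvERT. The section on the DIvERT intervention says that, if successful, it becomes part of the hospital's escalation process. Findings softened at the last step would carry into those decisions.

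Step 2 raises a related, smaller concern at the other end of the study. If fit with the designers' expectations influences which theories are prioritised, theories in which DIvERT fails may receive less attention when data are collected.

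**Working it through.** No arithmetic applies: the article gives no figure on this point. The check is to set the sections side by side.

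1. **Is alignment a stated goal, or only a loose phrase?** Step 5 uses the idea twice in consecutive sentences. Findings are aligned with the perspectives of those involved, and validation is said to ensure that results align with stakeholders' intentions. The first can be read as ordinary member checking. The second cannot, because its yardstick is intention and not experience.

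2. **Can the meeting change the output?** Yes. Objective 5 lists refining program theories among its purposes, so the alignment wording applies to a step that can alter what is reported.

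3. **Is it consistent with the other aims?** Suppose DIvERT does not work as intended in some context. Objective 4 and the opening of Step 5 require that this be reported, and Objective 5 asks the meeting to look for unintended consequences. A result that reports this departs from the intention. Both demands cannot be fully met for that result, so the sentence is in tension with its surroundings.

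4. **Does anything shown protect a disputed finding at that point?** The provisions for disconfirmation fall elsewhere:
   - The literature synthesis in Step 2, which may refute theories, precedes the designers' review.
   - Respondents may reject theories (Interviews), new themes may emerge (Who will be interviewed?), and data may refute theories or generate new ones (Qualitative data analysis). All of these belong to collection and analysis, before the closing engagement.
   - Academic supervisors meet fortnightly throughout (Qualitative data analysis), but no section gives them a rule for a finding that stakeholders dispute.

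5. **Does the Step 2 prioritisation matter later?** The introduction to Step 3 says the theories guide the choice of instruments and measurement tools. Staff survey says the questionnaire is built from them and used to confirm theory. Who will be interviewed? says participants are selected for their potential to help refine them. A theory given low priority may therefore have no question written to test it. Nothing in Step 2 says that theories contrary to the designers' expectations stay eligible, or that those set aside are listed.

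**The case against.** The strongest reply is that one badly worded sentence is being set against a protocol that otherwise invites disconfirmation. Much of this stands. Data collection is to capture intended and unintended outcomes (Data recording procedure and sample size). Theories can be refuted, and new ones added, after the designers have had their say. Step 5 itself calls for modest claims and for propositions that follow from the analysis. Stakeholders are not defined and could include ward clinicians with critical views. The before-and-after Code Grey comparison (Quantitative data analysis) does not depend on anyone's agreement.

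Three stronger readings are tempting, and the document does not support them.

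- **Designers alone choose what is tested.** Step 2 describes review and input in a collaborative step. It also lets designers suggest additional contexts, mechanisms or outcomes, which widens the set. Fit with their expectations is something they assess; it is not stated as a rule for exclusion.
- **Findings that contradict intentions will be revised.** That follows from a literal reading of the sentence, but no such procedure is described. The full protocol may hold a rule that the article omits.
- **Bias is built in and always favours DIvERT.** The provisions for refutation, new theories and unintended outcomes rule out so absolute a claim.

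The reply does not rescue the sentence itself. The safeguards act before the closing engagement or are silent about it, and the stated goal of that engagement is still alignment with intentions. This is a matter of what the article says, not of detail left to a longer document.

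**Conclusion.** The concern holds in a limited form. The Step 5 wording makes agreement with stakeholders' intentions a goal of validating the results. That creates a risk of bias towards the program's assumptions and is in tension with Objectives 4 and 5 and with Step 5's own undertaking to report failures. The Step 2 wording adds a lesser risk, because designers help prioritise theories while judging them against their own expectations, and those theories then shape the instruments and the survey.

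The direction of the risk is clear; its size cannot be quantified from the document. The conclusion rests on reading the Step 5 sentence as written, and on the absence, in the text shown, of any rule for disputed findings. Consulting designers and stakeholders is a legitimate part of the realist method described. The defect lies in the alignment criterion. The wording should be changed, but the design does not need to be.

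**What to change.** **Step 5.** Reword so that:
- stakeholder feedback is treated as further evidence on interpretation;
- a dated version of the findings is kept from before the interpretive meeting;
- a context-mechanism-outcome configuration changes only where collected evidence supports the change;
- disagreements between findings and stakeholder intentions are reported beside the findings.

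The dated version is a record and not a lock, so the meeting can still refine theories as Objective 5 intends.

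**Step 2.** State that:
- theories contrary to the designers' expectations stay eligible for testing;
- the researchers make the final selection after designer input;
- theories not taken forward are listed with reasons.

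A ban on removing any theory, or a compulsory rival for each one, is not needed to repair the text and would sit poorly with an iterative method.

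**Cost.** Revised wording, one dated document and a short log. No new data are required.

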## Conclusion

Currently, there is a lack of consistency in the early identification and management of patient MSD in acute hospital settings. In particular, the effectiveness of interventions in this area is not well understood. Furthermore, as reported staff feel unsafe, unsupported, and often under-skilled to manage patient MSD in acute hospital settings, which negatively impacts patient care and outcomes. The DIvERT intervention is a proactive model of care designed to initiate interventions at the first signs of deterioration. This is an effort to support the patient's journey by ensuring a timely appropriate plan of care and support clinical ward teams to identify and manage patient MSD proactively. This evaluation will help fill the knowledge gap on the effectiveness of interventions for managing patient mental state deterioration in acute medical settings. Additionally, findings from this research will offer opportunities to improve the clinical skills of staff through tailored training programs to assess, manage and escalate care for patients presenting with MSD effectively and safely. DIvERT is part of a comprehensive organisational initiative to identify and implement innovative strategies to minimise patient MSD, enhancing staff capability and resilience. In ending, in a continuously evolving health care environment, it is imperative to promptly incorporate new evidence-based interventions into clinical practice. This urgency is driven by the need to keep pace with evolving challenges and advancements, ensuring that patient care is continually improved. In trialling DIvERT, we trying to learn from the proposed realist evaluation to ensure that the rapid translation of the program not only optimises outcomes for our patients but also maximises impact at the organisational, service, and system levels. As a result of this flexibility in implementation, resources can be allocated more effectively, resulting in sustained improvements and adaptability within the broader healthcare framework.
